### Quality control

Because the *iCARE* patient app is not listed in the app store yet, patients cannot download and install the app by themselves. Therefore, those in the control groups are not accessible to the apps with full functions. Meanwhile, patients in the control groups are automatically putting on a waiting-list which offers the choice to allow them install the *iCARE*-1 at the end of the study. However, this study cannot avoid communications among patients who are discharged from the same hospital units. Whether or not the communication occurred will be determined by asking patients during their follow up. Should any contamination occurred, the patient will be eliminated.

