### Randomization and blinding

In this proposed study, three versions of *iCARE* apps will be installed on participant’s smart phone based on their group assignment (Additional file 1). Study investigators will assist participants in each group to download, register and log into the designated *iCARE* app:*iCARE*-1: is fully functional with individualized interventions delivered via multiple visual displays such as comics, videos, pictures, and text to address all the factors in the CAM model plus routine care;*iCARE*-2: is fully functional but all interventions are delivered only via text which did not address all factors in the CAM model plus routine care;*iCARE*-3: has limited function which only allows patients for daily data entry.

After baseline data collection, participants will be randomized to one of the three groups: the intervention group (*iCARE*-1 plus routine care), the control group 1 (*iCARE*-2 plus routine care), or the control group 2 (*iCARE*-3 plus routine care), following stratified block randomization. The randomization will be computer-generated by a statistician who will not have any active involvement in the study. The block size will be set at 15 with the allocation ratio set at 1:1:1 to ensure balance among three study groups. Participants will be stratified by 4 wards and their smoking status. The randomization assignment will be generated randomly, numbered consecutively, and will be kept in a sealed, opaque envelope. Patient assignment will be revealed to study researchers only after participants completed their baseline visit. This proposed study is an open-labeled trial as participants are fully aware of their intervention allocation, and the group assignments were known to study investigators. However, researchers who perform data analysis, and clinical staff who conduct laboratory testing will be unaware of the group assignment.

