### Sample size calculation and power analysis

Based on previous studies [3, 4, 52], we anticipated that the 3-year incidence rate for cardiovascular events is 10% for patient with CHD. We estimated that a total of 2256 participants (752 per group) would provide 80% power to detect a 40% relative reduction [53] in MACEs (the incidence of MACEs is 10% for the control group and 6% for the intervention group, hazard ratio is 0.6), with 2-sided testing and alpha set at 0.05, and following a Cox proportional hazards regression method. According to previous studies [34, 54] and based on our pilot study, we anticipated a maximum attrition rate of 20% among all enrolled patients. Therefore, a total sample size of 2820 participants (940 per group) are needed in the present study.

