### Data analyses

For baseline characteristics, categorical variables will be described as frequencies and proportions; continuous variables will be described as means and standard deviations, or medians and interquartile ranges where appropriate. Differences in baseline characteristics between the control and intervention groups will be detected using ANOVA test (continuous variables) or χ^2^ test (categorical variables) where appropriate.

Comparison of between group differences on the primary outcome will be performed according to both the intention-to-treat and the per-protocol principles. Simple χ^2^ analyses will be used to evaluate the main effect of the intervention on the MACEs at the end of the intervention period. Cox proportional hazards regression (with time to first event) will be used to estimate hazard ratios (HRs) comparing MACEs among three groups, by considering study group as an independent variable adjusted for covariates that are used for stratification (i.e., study sites, smoking status). The HRs and 95% *CI* will be calculated. Significant differences will be reported at the alpha level of 0.05 (two-sided).

All analyses related to secondary outcomes of the study are exploratory. The results of the analysis will be used to clarify the interpretation of the results related to the primary analysis, which include: changes in the proportion of adherence to health behaviors and medication, changes in anthropometry and biochemical parameters, etc. The mixed models and multilevel logistic regression models will be used to assess the differences in secondary outcomes between groups. Meanwhile, we will also explore whether the effects of intervention on the primary and secondary outcomes are consistent or not across subgroups of interest. Sensitive analyses will also be conducted.

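### Patients found contaminated at follow-up are to be eliminated, with no limit to the per-protocol set; this conflicts with the intention-to-treat analysis and can bias the primary comparison in either direction

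*Protocol article*

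**What the plan says.** Under Quality control, the protocol article explains that control patients cannot install the full-function app themselves, then concedes that "this study cannot avoid communications among patients who are discharged from the same hospital units". It continues: "Whether or not the communication occurred will be determined by asking patients during their follow up". The consequence is stated without qualification: "Should any contamination occurred, the patient will be eliminated".

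Under Data analyses, the commitment for the primary outcome is: "Comparison of between group differences on the primary outcome will be performed according to both the intention-to-treat and the per-protocol principles".

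Under Randomization and blinding, the trial is described as open-label: "participants are fully aware of their intervention allocation, and the group assignments were known to study investigators".

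The sample size section assumes that "the incidence of MACEs is 10% for the control group and 6% for the intervention group, hazard ratio is 0.6", and states that "a total of 2256 participants (752 per group) would provide 80% power to detect a 40% relative reduction". It then allows for at most 20% attrition, giving 940 per group. It does not say whether contamination removals count towards that 20%.

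**The concern.** An intention-to-treat comparison keeps every randomised patient in the assigned group. A patient eliminated for something that happened after randomisation cannot also be analysed as randomised, so the two sections cannot both be followed as they stand.

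The removal need not be neutral. Contamination is learned by asking, so a patient who has died or cannot be reached cannot report it. Patient and investigator both know the allocation, so what is reported and how it is judged may differ by arm. The section is concerned with control patients reaching the full app, so removals may fall mainly on the controls. If the removed patients differ in risk from those kept, the groups being compared are no longer the randomised groups.

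There is also a practical risk. The sentence sits among conduct instructions, so site staff could read it as a reason to stop follow-up. The primary outcome is collected through follow-up interviews to 36 months, and outcomes not collected then may be hard to recover for a later intention-to-treat analysis.

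**Working it through.** **The plan's own figure.** Inputs from the sample size section: 10% and 6% incidence, hazard ratio 0.6, two-sided alpha 0.05, Cox regression, 752 per group.

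- Expected events in one pairwise comparison: 752 × (0.10 + 0.06) = 120.3.
- Schoenfeld power: Φ(√(120.3/4) × |ln 0.6| − 1.96) = Φ(2.80 − 1.96) = 80.0%.
- Attrition: 752/0.8 = 940 per group and 2256/0.8 = 2820 in total.

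The stated sample size reproduces. The issue is the elimination rule, not the calculation.

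**Bias under no true effect.** The documents give no contamination rate, so these inputs are assumptions: 10% risk in both arms, 752 per arm before elimination, and elimination in the control arm only. Let c be the share of controls eliminated and r their risk relative to the control average.

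- Retained control risk: p = (0.10 − c × r × 0.10)/(1 − c).
- Apparent risk ratio: 0.10/p.
- Rejection rate: two-sided z test at 5%, comparing 752 patients at 10% with 752(1 − c) patients at p.

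Example with c = 0.20 and r = 0.5: p = (0.10 − 0.01)/0.80 = 11.25%, and the risk ratio is 0.10/0.1125 = 0.89. The difference is 0.0125. Its unpooled standard error is √(0.1125 × 0.8875/601.6 + 0.09/752) = 0.0169, so the shift is 0.74 standard errors and the rejection rate is 11.5%.

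| c | r | Retained control risk | Apparent RR | Rejection, unpooled | Rejection, pooled |
|---|---|---|---|---|---|
| 5% | 0.5 | 10.26% | 0.97 | 5.3% | 5.3% |
| 10% | 0.5 | 10.56% | 0.95 | 6.4% | 6.4% |
| 20% | 0.5 | 11.25% | 0.89 | 11.5% | 11.7% |
| 20% | 0.7 | 10.75% | 0.93 | 7.3% | 7.4% |
| 20% | 1.0 | 10.00% | 1.00 | 5.0% | 5.0% |
| 20% | 1.5 | 8.75% | 1.14 | 12.3% | 12.1% |

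A risk ratio below 1 favours iCARE-1; one above 1 counts against it. The pooled column corresponds to the planned χ² test.

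**Power at hazard ratio 0.6.** Assume elimination is unrelated to risk, affects controls only, and comes on top of the full 20% attrition. Events are 752 × 0.06 + 752(1 − c) × 0.10, and the allocation factor is (1 − c)/(2 − c)².

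- c = 10%: 112.8 events, factor 0.2493, power Φ(2.71 − 1.96) = 77%.
- c = 20%: 105.3 events, factor 0.2469, power Φ(2.60 − 1.96) = 74%.

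If actual attrition is lower, there may be no shortfall. With 10% attrition and 10% elimination, 940 × 0.9 × 0.9 = 761 remain, above 752.

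**The case against.** The strongest counter-argument is that the sentence can be read as an ordinary per-protocol exclusion. Data analyses promises both kinds of analysis, and analysis-set definitions are often left to a full protocol or analysis plan, which is not shown here. That reading is possible, but nothing in the text supports it: the sentence refers to the patient, names no set and stands outside the analysis section. A stated rule that conflicts with another stated rule is not a missing detail.

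A reader might go further and infer that the rule will produce a spurious benefit for iCARE-1, because those eliminated would be mostly event-free, motivated controls. The documents do not support that. Most components of the primary outcome are non-fatal, so patients with events can still be interviewed. At 10% risk, about 90% of all patients are event-free anyway. Patients readmitted for an event could meet other participants, which would make r greater than 1 and reverse the bias. Elimination of controls only is also an assumption, since the rule covers a patient in any arm.

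Nor does it follow that the numbers will be large because communication is unavoidable. The rule asks about communication but eliminates for contamination, and the article describes a barrier to obtaining the full app. At 5% eliminated the distortion is negligible.

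Finally, a loss of power is not certain. The 20% is described as a maximum and does not exclude these removals.

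**Conclusion.** The point holds as a conflict between two stated rules that affects the primary outcome. As written, elimination conditions the main comparison on a self-reported event after randomisation in an open-label trial, and the intention-to-treat commitment cannot be honoured for the patients removed. This does not depend on the direction of the bias.

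Neither direction nor size can be fixed from the documents. On the assumptions above, the effect ranges from negligible at 5% eliminated to a type I error of about 12% at 20% eliminated, in favour of iCARE-1 or against it depending on who is removed. It disappears if elimination is unrelated to risk. The fall in power to 77% or 74% applies only if the removals are additional to the full attrition allowance.

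**What to change.** Replace the sentence under Quality control with:

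> Patients reporting contamination remain in follow-up and in the intention-to-treat analysis in their randomised group; contamination is recorded with date and arm and used only in a predefined per-protocol or sensitivity analysis.

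Recruitment began in September 2019, so check whether anyone has already been eliminated. Where possible, recover their outcomes and restore them to the intention-to-treat set.

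Cost: one sentence and no additional patients; the planned 752 per group and 80% power stand. Real contamination will dilute the intention-to-treat estimate, by an amount that cannot be judged without a contamination rate. Recovering outcomes for patients already eliminated may take some site effort.

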### Process evaluation

Upon completion of the current study, process evaluation will be conducted to evaluate the feasibility of the mHealth intervention as recommended by researchers [55, 56]. The fidelity of intervention delivery, the exposure to the intervention, and feedback based on user’s experiences both from patients and nurses will be addressed in the process evaluation [56]. We will also ask patients to report on the reasons of non-adherent to health behaviors and medications during follow-up.

### Safety monitoring and event adjudication

Patients’ safety will be carefully monitored by a Data and Safety Monitoring Board from the *iCARE* research team. When there are adverse events occurred during the study, the time, place and cause of adverse events will be recorded. Potentially, vulnerable patients of the study are patients older than 75 years old and those with osteoporosis. Primary and secondary outcomes will be adjudicated by consensus among three investigators who are masked to the group assignments and results.

### Regulatory, data management and monitoring

The study will be conducted in accordance with the Good Clinical Practice, an international ethical and scientific standard for the design, conduct, performance, monitoring, auditing, recording, analysis, and reporting of clinical trial. Primary responsibility for data monitoring will be assumed by the principal investigator, who will oversee the integrity, security, and sharing of data, and take the primary responsibility for ensuring that the design of the study meets appropriate standards. Researchers will clean data collected through the *iCARE* system weekly, verify completeness and accuracy of the data.

### Confidentiality

Participants’ personal data will be replaced with research identification codes; files containing electronic data are password-protected and encrypted. The results will be disseminated in a deidentified manner for protecting the privacy and confidentiality of participants.

### Study status and recruitment

The participant recruitment process has started since September 2019 and is in progress. As recruitment is planned to be finalized in December 2022 and patients will be followed for 3 year, the final study results will be first available by December, 2025. Therefore, data cleaning or analyses are not yet started at the time of submission.

## Discussion

Individualized mHealth-based interventions represented a promising solution for facilitating adherence to health behaviors and medications, therefore, may decrease the burden of MACEs among patients with CHD. Although numerous studies have been implemented with individualized mHealth-based interventions, the long-term effects of such interventions on the reductions of MACEs have not been well established [24, 29, 30]. The influence of individualized mHealth-based interventions on MACEs was also not determined due to small sample sizes in previous studies [29, 30]. In the present study, the long-term effects of *iCARE* interventions on MACEs reduction in patients with CHD will be determined. In addition, previous study indicated that the challenges of CHD prevention were the maintenance of healthy behaviors [57]. The interventions of *iCARE* study were structured following the CAM model which focused on the moderators and mediators of the action and maintenance stages of behavioral change among patients with CHD [42]. The utilization of theory-driven interventions in the *iCARE* study may improve the likelihood of maintaining adherence to health behaviors [58]. If our *iCARE* study indeed demonstrates positive effects on patients with CHD, it will provide empirical evidence for supporting secondary preventive care in this population. Results will inform the design of future research focused on mHealth-based, theory-driven, intelligent, and individualized interventions for cardiovascular risk management.

## Data Availability

Data not applicable for a protocol. The results will be available to the public if necessary. The study findings will be disseminated via peer-reviewed publications and conference presentations.

## Abbreviations

ICARE: Individualized cardiovascular application system for risk elimination
ACS: Acute coronary syndrome
AMI: Acute myocardial infarction
BMI: Body mass index
CAM: Contemplation-action-maintenance
CHD: Coronary heart disease
CONSORT: Consolidated standards of reporting trials
CVD: Cardiovascular disease
FFQ: Food frequency questionnaire
FTND: Fagerström test for nicotine dependence
HRs: Hazard ratios
IPAQ: International physical activity questionnaire
MACEs: Major cardiovascular events
METs: Metabolic equivalents of task
MMAS-8: 8-Item Morisky medication adherence scale
PCI: Percutaneous coronary intervention
